## Methods and analysis

### Study setting

The study is a multicenter cross-sectional clinical trial, with activities related to the study performed at two sites (IRCCS Istituto Ortopedico Rizzoli, Bologna, Italy and Azienda Ospedaliero Universitaria Policlinico G. Rodolico-San Marco, Catania, Italy). This trial protocol was produced according to the Standard Protocol Items: Recommendations for Interventional Trials (SPIRIT) reporting guidelines (10).

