#### Inclusion criteria

Ø Healthy, osteopenic and OP (fractured and unfractured) patients;Ø Available DXA (hip and/or lumbar spine) BMD T-score;Ø Men or women > 40 years from two different Italian areas (Bologna, Catania);Ø Body Mass Index (BMI) between 18.5-29.9 Kg/m^2^;Ø Informed consent signed.

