#### Exclusion criteria

Ø Hematopoietic system diseases;Ø Bleeding disorders;Ø Infections (also positive for HIV-HBV-HCV);Ø Neoplastic pathologies;Ø State of pregnancy or breast-feeding;Ø Alcohol use (>20g alcohol per day currently or previously);Ø Smoking (>10 cigarettes per day currently or previously);Ø Diabetes.

Smoking and diabetes conditions were excluded to minimize major confounding effects on immune, metabolic, and inflammatory parameters that could interfere with the interpretation of PBMC behavior independently from bone status.

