### Allocation

Participants are stratified based on their bone mineral density (BMD), assessed by dual-energy X-ray absorptiometry (DXA) at the hip and lumbar spine. Stratification follows WHO criteria, resulting in three main groups:

- Osteoporotic patients (T-score < -2.5 SD), further divided into fractured and non-fractured subgroups;- Osteopenic patients (-2.5 SD < T-score < -1 SD);- Healthy controls (T-score ≥ -1 SD).

A total of 120 participants are enrolled, with 30 individuals allocated to each of the four resulting subgroups (osteoporotic fractured, osteoporotic unfractured, osteopenic, and healthy). Allocation is performed upon confirmation of DXA availability and based on T-score values. No randomization is applied, as group assignment depends on predefined diagnostic criteria.

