### Statistical methods

Statistical analyses are performed using R software (12) and relevant packages, such as ggplot2 (13), for graphical data visualization. A p-value < 0.05 is considered statistically significant.

A total sample size of 120 patients (n = 30 per group) was calculated using G*Power software (power = 0.80, alpha error probability = 0.05). The estimation was based on a Chi-square test (contingency table) with a medium effect size (w = 0.33), derived from the hypothesized difference in PBMC viability (yes/no) between healthy, osteopenic, and osteoporotic patients (fractured and non-fractured). A 20% potential drop-out rate was also considered in the calculation. This sample size ensures adequate statistical power for the primary outcome while maintaining feasibility across the two recruiting centers.

All data are recorded in an electronic dataset comprising continuous variables (e.g., age, PBMC viability, cell count and size, T lymphocyte subpopulation percentages, expression of pro- and anti-inflammatory cytokines, platelet-related parameters, and bone turnover markers, including BMD T-score), nominal categorical variables (e.g., gender, diagnosis), and ordinal categorical variables (e.g., patient stratification). Univariate analyses are conducted to assess the distribution, central tendency (e.g., mean, median), and dispersion (e.g., standard deviation, variance, interquartile range) of quantitative variables, and the frequency distribution of qualitative variables. Continuous variables showing skewed distributions are transformed to approximate normality.

After assessing normality and homogeneity of variances, appropriate statistical tests are applied. For normally distributed data with equal variances, parametric tests such as ANOVA, General Linear Models (GLM), and Student’s t-test are used. In cases of non-normality or heteroscedasticity, equivalent non-parametric tests (e.g., Kruskal–Wallis and Mann–Whitney U tests) are employed.

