Patients are stratified by BMD T-score and gender. Correlation, regression, and accuracy analyses are performed accordingly. Specifically, the relationship between BMD and PBMCs viability, count, size, differentiation, T lymphocyte subpopulations, inflammatory cytokines, platelet-related parameters, and serum biochemical markers of bone turnover is investigated. Pearson’s correlation coefficient is used for normally distributed data, and Spearman’s rank correlation is applied for non-parametric data. Receiver Operating Characteristic (ROC) curve analysis is conducted to assess the discriminative power of individual variables.

To avoid information loss and potential selection bias, missing values are imputed. When missingness is minimal, single imputation is used; otherwise, multiple imputations are performed, assuming data are missing at random (MAR) (14). Multiple imputation is conducted using the Multivariate Imputation by Chained Equations (MICE) package in R (15).

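### Age is recorded but no stated analysis uses it, so an age difference between the BMD groups may be read as test accuracy or as a marker–BMD association

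*Protocol article*

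**What the plan says.** **Design.** Under Inclusion criteria, the only age limit is a lower one: "Men or women > 40 years from two different Italian areas (Bologna, Catania". Under Allocation, the four groups of 30 follow from T-score and fracture status: "No randomization is applied, as group assignment depends on predefined diagnostic criteria". Neither section, nor Recruitment, describes matching or balancing on age.

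**Analysis.** Statistical methods names two stratifiers: "Patients are stratified by BMD T-score and gender. Correlation, regression, and accuracy analyses are performed accordingly". It plans Pearson or Spearman coefficients between BMD and each marker, and for accuracy: "Receiver Operating Characteristic (ROC) curve analysis is conducted to assess the discriminative power of individual variables". Group comparisons use ANOVA, GLM or t-tests, with Kruskal–Wallis or Mann–Whitney tests if the data are not normal or the variances are unequal. GLM and regression are named without covariates.

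**Data.** Age is recorded: "All data are recorded in an electronic dataset comprising continuous variables (e.g., age, PBMC viability, cell count and size". The categorical variables are given by example only, as "nominal categorical variables (e.g., gender, diagnosis), and ordinal categorical variables (e.g., patient stratification"; site is not among the examples. Study setting describes a "multicenter cross-sectional clinical trial, with activities related to the study performed at two sites".

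**Limitations.** BMI, comorbidities and substance use are named as confounders dealt with by exclusion. Age appears only as a limit on generalizability.

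**The concern.** The primary aim is the sensitivity and specificity of a PBMC-based test, judged across groups that are not randomised. The article itself links osteoporosis to age-related fractures and discusses bone changes in ageing men and women. An older mean age in the osteoporotic and fractured groups is therefore foreseeable, although no figure is given.

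If a marker also changes with age, it will separate the groups even when it says nothing about bone beyond age. A single-variable ROC cannot distinguish that case from a real bone signal. The same holds for a simple correlation with BMD, since two quantities that both move with age will correlate with each other. What is at stake is interpretation: a favourable AUC could be credited to the PBMC method when part or all of it could have been had from the date of birth.

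**Working it through.** **Inputs from the article.** Four groups of 30; two stratifiers (T-score and gender); ROC on single variables; age recorded; no age matching stated; age over 40 with no upper limit.

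**The plan's own figure.** The total of 120 rests on a chi-square test with w = 0.33, power 0.80, alpha 0.05 and 20% drop-out. With 3 degrees of freedom (four groups by yes/no), the noncentrality needed is 10.903, so N = 10.903 / 0.33² = 100.1. Taking 100 × 1.2 gives 120. The stated size is reproduced closely (strict rounding up gives 101, then 122). The point below does not depend on it; it only confirms the four-group layout.

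**Inputs assumed, because the documents do not give them.** Age difference d between the two groups compared: 5, 10 or 15 years. Within-group age SD s: 8 or 10 years. Within-group correlation ρ between marker and age: 0.2, 0.3 or 0.5. The marker carries no information on bone status once age is known.

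**Formula.** With the marker scaled to SD 1 within groups, the age gap shifts its mean by ρ·d/s. For two normal distributions with equal variance:

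crude AUC = Φ( ρ·(d/s) / √2 )

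Examples:
- d = 5, s = 10, ρ = 0.2: Φ(0.10/1.414) = 0.53
- d = 10, s = 10, ρ = 0.3: Φ(0.30/1.414) = 0.58
- d = 15, s = 8, ρ = 0.5: Φ(0.9375/1.414) = 0.75

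| Age gap (years) | SD | ρ = 0.2 | ρ = 0.3 | ρ = 0.5 |
|---|---|---|---|---|
| 5 | 10 | 0.53 | 0.54 | 0.57 |
| 5 | 8 | 0.53 | 0.55 | 0.59 |
| 10 | 10 | 0.56 | 0.58 | 0.64 |
| 10 | 8 | 0.57 | 0.60 | 0.67 |
| 15 | 10 | 0.58 | 0.62 | 0.70 |
| 15 | 8 | 0.60 | 0.65 | 0.75 |

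If d = 0 or ρ = 0, the AUC is 0.50. An age-adjusted AUC is 0.50 in every cell.

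**Group comparisons.** Four groups of 30, age SD 8, no bone effect beyond age, ρ = 0.1 / 0.2 / 0.3, 4,000 simulated trials per setting:
- Assumed mean ages 58/60/64/70: unadjusted ANOVA rejects at the 5% level in 7% / 15% / 31%, and Kruskal–Wallis in 7% / 14% / 29%.
- Assumed mean ages 55/60/66/74: ANOVA 10% / 33% / 67%, and Kruskal–Wallis 9% / 31% / 65%.
- With age as a covariate, rejection returns to 5% throughout.

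Switching to rank tests gives almost no protection.

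**Correlations.** If marker and BMD are related only through age, their crude correlation equals the marker–age correlation times the BMD–age correlation. The partial correlation given age is zero.

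**The case against.** The strongest reply is that this argues from silence. GLM and regression are planned, their covariates are not listed, age is not excluded, and an article may leave a covariate list to a full protocol or SAP. That stands for GLM and regression: the article does not say that age is kept out of them. It does not dispose of the point, because the correlation and ROC methods are specified, and as specified (simple coefficients, individual variables) they are unadjusted. The fallback rank tests named for the group comparisons take no covariate either.

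Second, a crude ROC is the direct answer to a question about sensitivity and specificity; adjustment answers a different one, namely what the test adds. That also stands, and it is why the crude ROC should stay. Third, age alone gives only modest AUCs over most of the range. True, but a modest spurious part can still reach significance or inflate a real signal.

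Some stronger readings are tempting but not supported:
- **That age differences will appear as accuracy.** This needs both an age gap and an age–marker association, and the documents give figures for neither.
- **That site is recorded and biases the results.** Site is not among the example variables, and it would bias accuracy only if the group mix differed between sites, which is not reported.
- **That the analysis breaks a stated aim to remove confounding.** The phrase "minimize major confounding effects on immune, metabolic, and inflammatory parameters" explains only why smoking and diabetes are excluded.
- **That bone-active drugs or steroids confound the groups.** The exclusion list has no line on them, but the CRF is not shown and the documents say nothing about their use by group.

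**Conclusion.** The point holds as a possible bias that the stated plan does not address. Neither the design nor the named correlation and ROC methods control for age, and age is available in the dataset. Under the assumed ranges, age alone yields an AUC of about 0.53 to 0.75; the upper end needs a 15-year gap, an SD of 8 and a correlation of 0.5. If the groups turn out to have similar ages, or the marker is unrelated to age, there is no bias. The four-group rejection rates are for a continuous marker and were not worked out for the yes/no viability comparison behind the sample size. The change should be made before analysis, since it is nearly free and settles how a favourable result can be read.

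**What to change.** In Statistical methods, keep the crude ROC for sensitivity and specificity and add:

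1. Age and sex as covariates in the GLM and regression models, with site as a two-level factor.
2. Age-adjusted partial correlations of each marker with BMD, beside the simple ones.
3. Either an age- and sex-adjusted ROC, or the gain in AUC of the marker over a model with age plus sex.

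Report age by group so that readers can judge the gap.

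The cost is a few model degrees of freedom among 120 participants, and adjusted accuracy may be lower than crude accuracy. No additional patients are needed. Site has only to be available as a variable for each participant.

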### Intervention

An overview of the study design and analytical workflow is shown in **Figure 1**. Healthy, osteopenic, and osteoporotic (fractured and non-fractured) patients of both sexes, with available DXA or, for fractured patients, DXA prescribed as per clinical practice for secondary prevention, are enrolled during outpatient visits and/or upon admission to the emergency department and/or hospital, after signing written informed consent. Subsequently, a blood sample (2–5 mL) is collected from each enrolled patient and used for PBMC isolation, performed through density gradient centrifugation, and for serum collection. Once isolated, a portion of PBMCs is cultured *in vitro* (without differentiation factors normally required for PBMCs viability maintenance and differentiation) to assess their viability, number, size, and differentiation into osteoclasts. PBMCs viability are evaluated using optical microscopy and the Alamar Blue assay (a non-toxic reagent that assesses cellular activity through the chemical reduction of resazurin to resorufin in the mitochondria of living cells) at 48, 72, and 96 hours and at 1 and 2 weeks. At the same time points, PBMCs number and size (diameter in µm) are also assessed. Finally, at 2 weeks, spontaneous osteoclastogenesis, i.e., the ability of PBMCs to spontaneously become osteoclasts, is evaluated and quantified through immunocytochemical analysis (Tartrate-Resistant Acid Phosphatase - TRAP - staining) and gene expression analysis *via* RT-PCR (Tumor Necrosis Factor alpha - TNF-α, Receptor Activator of Nuclear Factor κB Ligand – RANKL, Macrophage Colony-Stimulating Factor - M-CSF, Parathyroid Hormone - PTH). Differences in PBMCs viability, number, size, differentiation, and/or activity are also be analyzed considering gender differences. To achieve the secondary objectives of the protocol, a PBMCs aliquot undergoes immunophenotypic characterization to identify the T lymphocyte cell phenotype and evaluate its subpopulations. Specifically, the Th1 (CXCR3, CCR5), Th2 (CRTH2, CCR4, CCR3), Th17 (CCR6 and RORC), and TReg (CD25, CD26, CD127low) subpopulations are analyzed by flow cytometry. Biochemical levels of pro- and anti-inflammatory cytokines are assessed in serum samples from enrolled patients (interleukin (IL)-1, IL-2, IL-3, IL-4, IL-5, IL-9, IL-10, IL-17, IL-21, IL-22, IL-33, TNF-α, Interferon gamma - IFN-γ). Moreover, serum samples are also used to evaluate key markers of bone turnover, including bone-specific alkaline phosphatase, procollagen type I N-terminal propeptide (markers of bone formation) and N- and C-terminal telopeptides of collagen I (markers of bone resorption).

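### The imputation rule makes no exception for cell diameter and differentiation time that do not exist because a culture did not survive

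*Protocol article*

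**What the plan says.** Three parts of the protocol article bear on this point.

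- **Imputation (Statistical methods).** The rule is general: "To avoid information loss and potential selection bias, missing values are imputed". There are two branches. The first reads "When missingness is minimal, single imputation is used", and the second reads "otherwise, multiple imputations are performed, assuming data are missing at random (MAR"), with MICE in R. No variable and no reason for missingness is exempted.
- **Expected non-viability (Intervention; Statistical methods).** Cells are cultured "without differentiation factors normally required for PBMCs viability maintenance and differentiation". The effect size for the sample size is "derived from the hypothesized difference in PBMC viability (yes/no) between healthy, osteopenic, and osteoporotic patients (fractured and non-fractured").
- **What is measured, and when (Intervention).** Viability has five reading times, the first at 48 hours and the last at 2 weeks. Cell number and size follow this schedule: "At the same time points, PBMCs number and size (diameter in µm) are also assessed". Osteoclast formation is read once, at the end: "Finally, at 2 weeks, spontaneous osteoclastogenesis, i.e., the ability of PBMCs to spontaneously become osteoclasts, is evaluated and quantified", by TRAP staining and RT-PCR.

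The primary objective lists viability, number, size and differentiation time together and aims at sensitivity and specificity. Size and differentiation also enter the T-score correlations, and ROC analysis is applied to individual variables. The article does not say how size or differentiation is recorded for a non-viable culture.

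**The concern.** Imputation under MAR suits a value that exists but was not observed. The diameter of cells in a culture that has died is not such a value, and neither is the differentiation time of a culture that never differentiated. These blanks arise from the outcome under study, and the plan expects them at rates that differ by group. Putting viability into the imputation model does not help: no non-viable culture has an observed diameter or differentiation time, so every filled value is extrapolated from survivors.

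At stake are two of the four measures in the primary objective, and possibly the RT-PCR readings. Their group comparisons, correlations with T-score and ROC curves would rest partly on invented values. The share invented would differ between the groups being compared.

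**Working it through.** **1. The plan's own figure.** Inputs from Statistical methods: w = 0.33, alpha 0.05, power 0.80, four groups, viability yes/no, 20% drop-out. Degrees of freedom = (4 − 1)(2 − 1) = 3, which needs a noncentrality of 10.903. N = 10.903 / 0.33² = 10.903 / 0.1089 = 100.1, and 100.1 × 1.2 = 120.1. The stated 120 is reproduced, so the sample size does rest on a four-group viability contrast. It does not depend on the imputation rule.

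**2. How many cultures could be affected.** The article gives no viability rates, and w alone does not fix them. For equal groups, w² = (variance of the group rates) / [p̄(1 − p̄)].

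- *Fewest failures compatible with w = 0.33:* all in one group, with failure rate q. Then w² = (3q²/16) / [(q/4)(1 − q/4)] = 0.75q / (1 − 0.25q) = 0.1089, so q = 0.1089 / 0.7772 = 0.14. That is 0.14 × 30 = about 4 of 120 cultures.
- *Example with failures in all groups:* viability 20%, 50%, 60% and 60% gives w = 0.328. Failures are 24 + 15 + 12 + 12 = 63 of 120.

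The number therefore runs from about 4 to more than half, if 'not viable' means that nothing can be measured.

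**3. Effect on a differentiation measure left blank in failed cultures.** All inputs are assumed: two groups of equal size, and a true score of zero (no differentiation) in failed cultures.

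| Viability | Survivor means | Failed scored as none | Imputed, group in model | Imputed, group left out |
|---|---|---|---|---|
| 35% v 65% | 10 v 10 | 6.5 − 3.5 = 3.0 | 0.0 | 0.0 |
| 20% v 80% | 10 v 10 | 8.0 − 2.0 = 6.0 | 0.0 | 0.0 |
| 35% v 65% | 10 v 12 | 7.8 − 3.5 = 4.3 | 12 − 10 = 2.0 | 0.91 |

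For the last cell, the pooled survivor mean is 3.5 + 7.8 = 11.3. The filled group means are 3.5 + 0.65 × 11.3 = 10.845 and 7.8 + 0.35 × 11.3 = 11.755, a difference of 0.91. Simulation with 30 per group and a survivor SD of 2 agrees: 2.98 becomes 0.01 in the first row, and in the third row 4.36 becomes 1.99 with group in the model and 4.27 becomes 0.89 without it.

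**4. Effect on diameter.** Here there is no true value for a failed culture, and zero is not a diameter. At 35% v 65% viability with 30 per group, 19.5 and 10.5 diameters on average would be invented, 30 of 60 in all. With group in the model, the mean difference stays at the survivors' difference (2.0 in the third row). With group left out, it shrinks to 0.91. Either way the result would be presented as applying to all participants although it is conditional on viability.

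**The case against.** The strongest reply is that the rule covers missing values only, and nothing says that a failed culture is recorded as missing. Much of what is measured can be read in a dead culture. A low Alamar Blue signal is data, a cell count of zero is a result, and so is the absence of TRAP-positive cells. Viability also appears among the continuous variables in Statistical methods, so yes/no may be a cut-off on a graded reading, with cells still present and measurable below it. For diameter, imputation with group in the model returns the same mean difference as an analysis of viable cultures. Coding details are also commonly left to the CRF or the analysis plan.

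Most of this stands, and it limits the point:

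- A reader might infer that the group difference driving the design is erased. It is not: viability is observed in failed cultures.
- A reader might infer that everything is imputed under MAR. That assumption is stated only for the multiple-imputation branch. Single imputation has no stated mechanism, though filling from survivors would be just as unsuitable there.
- The table in step 3 applies only if differentiation is left blank. If it is entered as zero, that loss does not occur.

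What does not fall away is diameter and differentiation time, and possibly RT-PCR expression. These have no natural zero, so a blank is the likely entry, and the rule as published would fill it. The point corrects a stated rule and does not ask for omitted detail.

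**Conclusion.** The point holds in a conditional form. If values that are undefined because a culture failed or did not differentiate are treated as missing, the published rule replaces them with values from surviving cultures. This removes or attenuates the part of the group contrast, T-score correlation and ROC result that runs through viability. A difference among survivors can remain, wholly if group is in the imputation model and in part if it is not.

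The size cannot be fixed from the article. On assumed inputs the loss is complete when survivors do not differ (3.0 to 0.0, or 6.0 to 0.0) and partial when they do (4.3 to 2.0 or 0.91). The conclusion rests on two things that the article leaves open: that such readings are coded as missing, and that a non-viable culture has no measurable cells. The viability yes/no contrast, zero cell counts and the total of 120 are not affected. The change is worth making because it is cheap and concerns measures named in the primary objective.

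**What to change.** Add to the imputation paragraph that values undefined because a culture did not survive or did not differentiate are not imputed, in either branch. Then:

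- record differentiation in such cultures as none: zero TRAP-positive cells, and differentiation time as not reached by 2 weeks;
- analyse diameter among viable cultures only, and label the result as conditional on viability;
- limit imputation to technical or administrative loss, such as a lost or haemolysed sample;
- add a reason-for-missing field to the CRF so that the two kinds of blank can be told apart.

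The cost is about two sentences and one CRF field. The downside is fewer complete diameter records at the late time points. Enrolment began on 30 August 2024, so for participants already sampled the reason would have to be taken from laboratory records where these allow it.
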